### Strategies to improve adherence to interventions {11c}

Protocol adherence is handled by the first and second author with assistance from a research assistant who secures that all required questionnaires and all items of information are entered into the Research Electronic Data Capture (REDCap) 8.5.22 2019 Vanderbilt University system.

### Relevant concomitant care permitted or prohibited during the trial {11d}

This study is an add on to relevant concomitant treatment, which is allowed during the study period. Concomitant treatment includes sessions with the primary contact nurse to evaluate the effect of pharmacotherapy. Participation in other psychiatric research interventions during the intervention period is prohibited. Treatment with hypnotics are allowed during the study and will be registered. The hypnotics-use in both groups will be compared statistically to test for significant differences.

### Provisions for post-trial care {30}

Any harm to patients from attending the trial is covered by the Danish patient reimbursement scheme. After the trial has concluded, patients will continue their usual treatment.

### Outcomes {12}

#### Primary outcome

Changes in the quality of sleep measured by the Pittsburgh Sleep Quality Index (PSQI) [37].

Data are obtained by questionnaires at inclusion (baseline/week 0), at week 2, and at week 6.

#### Secondary outcomes

Changes in SE are measured daily during the 6-week study period. SE changes are calculated by measurements from actigraphy and registrations in sleep diaries. More specifically, SE is calculated as; total sleep time (TST)/time in bed (TIB) × 100. In the actigraphy data, TST is calculated by the Motionware software, and TIB is defined as the period from the patient presses the event marker at “lights out” until they get out of bed (time registered in the sleep diary). The calculation of SE based on sleep diary data is based on the TST and TIB registered by the patient in the sleep diary.SOL changes. SOL is the length of time it takes to accomplish the transition from full wakefulness to sleep, and it is measured daily during the 6-week study period. SOL is calculated based on the patient's registered bedtime (“lights out”) marked by the event marker and the first sleep onset measured by actigraphy. In sleep diaries, SOL is calculated based on the patient's registered bedtime (“lights off”) and their registered fell-asleep-time.Changes in WASO are measured daily during the 6-week study period. WASO changes are calculated by measurements from actigraphy as the difference between assumed sleep and actual sleep time. Furthermore, WASO is calculated based on patients’ registrations in sleep diaries, where they report how long their nocturnal awakenings last.Changes in the number of NWAKE are measured daily during the 6-week study period. NWAKE is calculated by measurements from actigraphy (called “wake bouts”) and based on the sleep diaries where patients register the number of NWAKE. The night-time sleep frame in actigraphy data is defined as sleep occurring during a 16-h night interval (from 20:00 h to 11:59 h). The investigators designate the first sleep episode after 8PM as the first nocturnal sleep episode. If the individual is already asleep at that time, the bedtime will be moved earlier to the first wake epoch preceding sleep onset. If the individual is still asleep after 11:59PM, wake time will be moved to the first subsequent epoch of activity.Changes in the subjective appraisal of insomnia severity. Data are measured by questionnaires at inclusion (baseline/week 0), at week 2, and at week 6 (endpoint). The insomnia severity status is measured by the Insomnia Severity Index (ISI) [38].Changes in the subjective experience of well-being. Well-being is measured at inclusion (baseline/week 0), at week 2, and at week 6 (endpoint) by the WHO-5 Well-Being Index (WHO-5) questionnaire [39].Changes in level of personal recovery. These changes are measured at inclusion (baseline/week 0), at week 2, and at week 6 (endpoint) by the INSPIRE-O questionnaire [40].Changes in work ability are measured at inclusion (baseline/week 0), at week 2, and at week 6 (endpoint) by the Work Ability Index [41] questionnaire.Changes in the consumption of sleep medication are registered daily during the 6-week study period. Daily use of sedatives and hypnotics will be measured by registration of medication use in sleep diaries and registrations in the electronic health record made during the study period [time frame: 6 weeks = 42 days]. The investigators will measure the change in total use of regular and per-need sedatives and hypnotics in mg.

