### Sample size {14}

A power calculation was performed based on the results of a similar study [28] with PSQI as a secondary outcome using an average effect size of 0.67. Assuming a power of 0.80, a significance level of 0.05, and an expected power magnitude of 0.67, a sample size of *n* = 44 is obtained for each group. The expected 25% dropout rate is based on former experiences from a pilot project (*n* = 55). A total of 88 patients will be included in the study.

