#### Data management {19}

The following data will be collected:From the patients and their hospital records: name, phone number, personal identification number from the Danish Civil Registration System (“CPR number”), diagnosis, and medication prescriptions. The following additional data are included through a semi-structured assessment interview at inclusion: marital status, employment status, level of education, consumption of tobacco, alcohol, other drugs, previous treatment for sleep problems, and exposure to daylight are collected.From actigraphy (Actiwatch MotionWatch 8 from CamNtech Ltd, Cambrigde UK): SE, SOL, WASO, and NWAKE. The MotionWatch 8 is a wrist-worn activity monitoring device, similar in size to a watch, with a tri-axial accelerometer. It has a 4.0 Mbits of storage capacity and a waterproof casing. It is used to objectively monitor movement during sleep. For sleep scoring, a tri-axial accelerometer is used to monitor body movements. For differentiating between sleep and wake epochs, the MotionWare Software (version 1.2.28, CamNtech, Ltd.) is used. This device uses an algorithm that depends on thresholding, assigning an activity score to each epoch by totalizing the epoch in question and those surrounding it using weighting factors. If the activity score of an epoch is above a predefined threshold, the epoch is scored as wake; otherwise, it is scored as sleep. A 30-s epoch is used in this study. Patients are asked to wear the actigraph 24 h a day on their non-dominant wrist during the 6-week study. Patients are instructed to press the event-marker when they intend to sleep (“lights out”) and when they experience their final wake up in the morning. Sleep diaries are used to validate sleep and wake onset if the patients forget to press the eventmarker. The first author and an experienced sleep scientist will perform the scoring and analyze the actigraphic records. The degree of agreement between raters in ten scorings will be calculated and reported using the intraclass correlation coefficient.From sleep diaries: The use of sleep medication “as needed”, bedtime (“lights out”), sleep onset, wakeup time and time for getting out of bed, SE, SOL, WASO, NWAKE, daytime naps including lengths (Additional files 2 and 3: Sleep and medication diary for the intervention and control group).From six validated questionnaires:The ISI measures the subjective experience of insomnia severity. The scale ranges from 0 to 28. The higher the score, the more severe the insomnia [38].The PSQI measures sleep quality [37]. The score ranges from 0 to 21, “0” indicating no difficulty and “21” indicating severe difficulties.The WHO-5 describes well-being (38). The questionnaire measures well-being on a scale ranging from 0 to 100. The higher the score, the more well-being.The INSPIRE-O consists of five short questions that measure personal recovery [40]. The questionnaire measures personal recovery on a scale ranging from 5 to 25. The higher the score, the more recovery.The Work Ability Index, a questionnaire measuring work ability [41]. A score of 0 shows the lowest possibility that the person would take on a job; a score of 10 denotes the highest probability.The International EQ-5D-5L questionnaire estimates quality-adjusted years of life. The questionnaire is applied to estimate quality-adjusted years of life [42].

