
All patients complete the six validated questionnaires at personal visits at baseline (week 0) and again after 2 and 6 weeks. Patients are asked to wear actigraphs around the clock during all 6 weeks and to complete a short sleep diary on a daily basis (see Additional files 2 and 3). Furthermore, they complete the morningness-eveningness questionnaire (MEQ) at week 2 to estimate their chronotype. This validated questionnaire has scores ranging from 16 to 86. Scores of 41 and below indicate “evening types.” Scores of 59 and above indicate “morning types.” Scores between 42 and 58 indicate “intermediate types” [43]. For the study schedule used for enrolment, intervention, and assessments, please see Table 1.

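### The sleep-medication outcome is a total in mg with no denominator of observed days, so missing diary days and early dropout understate as-needed use

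*Protocol article*

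**What the plan says.** All references are to the protocol article.

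- **Summary measure** (Outcomes {12}, Secondary outcomes): "The investigators will measure the change in total use of regular and per-need sedatives and hypnotics in mg". The sentence before it sets the frame: "time frame: 6 weeks = 42 days". No per-day or per-observed-day denominator is given.
- **Sources** (same section): "Daily use of sedatives and hypnotics will be measured by registration of medication use in sleep diaries and registrations in the electronic health record".
- **What each source supplies** (Data management {19}): the list of items taken from patients and hospital records includes "diagnosis, and medication prescriptions". The diary list opens with "From sleep diaries: The use of sleep medication “as needed". All patients are asked "to complete a short sleep diary on a daily basis".
- **Expected loss** (Sample size {14}): "The expected 25% dropout rate is based on former experiences from a pilot project".
- **Patients who stop** (section {18a}): they are asked for questionnaires, with the PSQI and ISI first. Recovery of diary or medication data is not mentioned.
- **Analysis** (sections {20a} and {20c}): intention to treat, with a likelihood-based mixed model under missing at random for the continuous outcomes. Time has three levels: baseline, week 2 and week 6.

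**The concern.** A prescription in the health record does not show whether an outpatient took an as-needed tablet on a given night. In practice only the diary shows that. If the outcome is a plain sum of recorded milligrams, a night without a diary entry adds nothing, and neither does any night after the patient has left. A patient who stops the diary and a patient who stops the drug then produce the same figure.

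The other diary outcomes (sleep efficiency, onset latency, wake after sleep onset, awakenings) are nightly quantities, so a blank night simply contributes no value. The medication outcome is the only one worded as a total, so it is the only one that shrinks when a night is unrecorded.

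The hypothesis for this outcome is a reduction, and section {11d} promises a comparison of hypnotic use between the groups. What is at stake is whether a fall in recorded milligrams can be read as a fall in use.

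**Working it through.** **The plan's own figure.** 6 weeks × 7 days = 42 days, as stated. The article gives no other number for this outcome.

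**Inputs**

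- Frame: 42 days (Secondary outcomes).
- Dropout d = 0.25 (Sample size {14}).
- Leaving times spread evenly over the frame, so a leaver is observed for half of it on average: assumption.
- Diary completion c while in the study: not given; taken as 100%, 90% and 80%.
- Unrecorded days add nothing to the sum: the consequence of an unadjusted total, not a rule in the text.

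**1. Share of as-needed use that reaches the total**

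Observed share = c × [(1 − d) + d × 0.5]. With d = 0.25 the bracket is 0.75 + 0.125 = 0.875.

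| Diary completion | Observed share | Understatement |
|---|---|---|
| 100% | 0.875 | 12.5% |
| 90% | 0.788 | 21% |
| 80% | 0.700 | 30% |

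If all leavers go on one day instead, the understatement with full diaries is 0.25 × (1 − day/42): 16.7% at day 14, 12.5% at day 21 and 8.3% at day 28.

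**2. Dilution by regular medication.** These percentages apply to as-needed use only. If regular use is fully recovered from the health record, the shortfall in the combined total is the as-needed share times the as-needed shortfall. At 80% completion and no dropout that is 0.25 × 20% = 5% when as-needed drugs are a quarter of the milligrams, and 20% when they are all of them (shares assumed).

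**3. Between arms, same true use**

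- Equal completion and dropout: both as-needed totals shrink by the same factor, so their ratio stays at 1.00.
- Completion 95% in the intervention arm and 80% in the control arm (assumed), dropout 25% in both: 42 × 0.95 × 0.875 = 34.9 days against 42 × 0.80 × 0.875 = 29.4 days. The ratio is 0.842, so control use looks 16% lower.
- Dropout 35% in one arm and 15% in the other (assumed), full diaries: 0.825 / 0.925 = 0.892, so the first arm looks 11% lower.

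**4. Does the mixed model help?** It handles an outcome value that is absent. A patient with 25 of 42 diary days still has a total, and the model takes it as fully observed. The gap lies inside the value, where missing at random does not reach.

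**5. Change over the planned time points.** Totals between visits would cover 14 days (weeks 0–2) and 28 days (weeks 2–6). At constant daily use the second is 28/14 = 2 times the first. A single 42-day total has no earlier value to change from.

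**6. With a mean per observed day.** Equal true daily use gives an arm ratio of 1.00 at any completion rate that is unrelated to use.

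**The case against.** The strongest reply is that the article nowhere says blank days are zeros. The word total may mean regular plus as-needed drugs taken together, not a sum over 42 days, and the 42-day bracket belongs to the sentence on daily registration. Handling of blank diary days and minimum diary days is commonly left to an analysis plan, which is not at hand. If incomplete windows were set to missing, the planned model would treat them in the ordinary way.

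Much of this stands. A reader might infer that the plan counts dropout and blank diaries as reduced consumption; the text does not say so. The narrower point survives because the article does state a summary measure, in mg and as a total, and that measure has no denominator. Even if total means both drug types combined, the amount must still be accumulated over some set of days, and that set is not tied to the days observed.

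The health record is also a named source. Regular use therefore need not depend on the diary, and the percentages in table 1 must not be read as applying to the whole outcome.

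A reader might also infer that the comparison between arms is biased, because the intervention arm has six visits and the control arm three (Discussion). The documents do not establish this: all patients are asked for a daily diary, and no completion or dropout rate by arm is given. If completion were better in the intervention arm, the error would make control use look lower, which works against the hypothesis.

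**Conclusion.** The concern holds as a weakness in the stated definition. A total in mg without observed days as denominator understates as-needed use when diary days are missing or patients leave early, and the mixed model does not undo that. With the plan's 25% dropout and evenly spread leaving times (assumption), the understatement of the as-needed component is 12.5% with full diaries and 30% at 80% completion (assumption). It is smaller for the combined outcome to the extent that regular use is recovered from the health record.

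A biased arm comparison is not shown. With equal missingness the as-needed ratio is unchanged, although totals and differences in mg still shrink. The 16% and 11% arm differences illustrate assumed imbalances and are not predictions. The unequal 14-day and 28-day intervals are a separate reason not to use totals, and that reason needs no assumption about missing data. This is one secondary outcome and the primary analysis is unaffected, but the definition should be corrected before the data are analysed.

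**What to change.** Replace the total by mean daily use per observed day, in mg, in each analysis window:

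- **As-needed drugs:** the sum over completed diary days divided by the number of those days. A completed day with no as-needed drug recorded counts as zero. A blank day, or a day after withdrawal, counts as missing.
- **Regular drugs:** taken from the health record for the days the patient is under observation, divided by those days.
- **Outcome:** the sum of the two daily means, compared between windows and arms with the planned mixed model. Report the number of observed days by arm and window, so that readers can see whether missingness was balanced.

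The cost is a short change to the outcome definition and to the analysis code, with no new data. There are two drawbacks. Patients with few diary days contribute noisier means. The mean is also unbiased only if missing days are unrelated to use given the model, so it reduces dependence on diary completeness without removing it.

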### Objectives {7}

The aim of the study is to investigate the efficacy of a transdiagnostic sleep intervention for patients with sleep problems comorbid to bipolar disorder, unipolar depression, or attention deficit disorders.

The primary hypothesis is that the transdiagnostic sleep intervention improves sleep quality compared with a control group receiving brief sleep hygiene education.

The secondary hypotheses are that a transdiagnostic sleep intervention increases subjective and objective sleep efficiency (SE), reduces sleep onset latency (SOL), wake after sleep onset (WASO), and nocturnal awakenings (NWAKE); and that it reduces the severity of insomnia, while increasing well-being, personal recovery, and work ability. Furthermore, participation in the intervention is expected to result in a reduction in the consumption of sleep medication compared with a control group receiving short sleep hygiene education.

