### Statistical methods

#### Statistical methods for primary and secondary outcomes {20a}

Demographic and clinical data used to compare the intervention and control group will be analyzed using descriptive statistics. Categorical variables will be reported using proportions, whereas means and standard deviations will be reported for continuous variables. Fisher’s exact test and Student’s *t*-test are applied to test for the difference between the intervention and control group for categorical and continuous variables. The intent-to-treat method will be used to examine if a significant change in the ISI and PSQI total scores from baseline to 6 weeks can be established.

To compare the differences in measurements between the intervention and control group over time, we will apply a linear mixed effects (LME) model, which is recommended for longitudinal data with missingness [45]. The “maximum likelihood estimation” assuming “missing at random” for data is used to examine the primary and secondary continuous objectives. The fixed components of the model are gender, age, time variable (1: baseline, 2: 2 weeks, 3: 6 weeks), type of treatment (1: intervention group, 2: control group), and the interaction between the time variable and the type of treatment. Means, standard deviation, 95% confidence interval, power magnitude, and the average reduction over time and *p*-value for reduction in the primary and secondary outcomes will be calculated from the model. All statistical analyses will be performed using Stata version 15., R-Studio, or SPSS version 20.0.

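### Adding up milligrams of different sedatives and hypnotics weights each patient by drug strength and counts a drug switch as a change in consumption

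*Protocol article*

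**What the plan says.** Under Secondary outcomes, the protocol article describes the source of the data: "Daily use of sedatives and hypnotics will be measured by registration of medication use in sleep diaries", together with entries in the electronic health record, over a stated period ("time frame: 6 weeks = 42 days"). It then fixes the variable: "The investigators will measure the change in total use of regular and per-need sedatives and hypnotics in mg". That sentence sets the unit (mg), the aggregation (a total) and the scope (two drug classes, scheduled and as-needed use together).

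The variable serves an efficacy hypothesis. Objectives {7} states that "participation in the intervention is expected to result in a reduction in the consumption of sleep medication", relative to control. The section on concomitant care {11d} names no agent ("Treatment with hypnotics are allowed during the study and will be registered") and promises a test: "The hypnotics-use in both groups will be compared statistically to test for significant differences".

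Nothing in the article limits the outcome to one drug, analyses drugs separately or converts them to a common unit.

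**The concern.** One usual dose of one sedative may be a few milligrams and one usual dose of another many times that. If both go into one sum, two things follow.

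- **Weighting.** A patient who gives up one dose a week of a high-mg drug moves the group mean far more than a patient who gives up one dose a week of a low-mg drug, although both have cut one dose.
- **Switching.** A patient who moves from a high-mg to a low-mg drug and takes just as many doses appears to have cut consumption sharply. The reverse switch looks like a sharp increase.

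More than one drug is to be expected. Patients have three different diagnoses, come from several clinics and two municipal services, and may continue any concomitant treatment. What is at stake is whether the test of the medication hypothesis is as informative as the data allow, and whether a difference, or its absence, could come from drug mix and switching instead of from the amount taken.

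**Working it through.** The article states no figure for this outcome, so there is none to reproduce. What follows is an illustration under stated assumptions.

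**Inputs from the protocol article.** 44 patients per group and 25% expected dropout (Sample size {14}), so 44 × 0.75 = 33 per arm. Two-sided 5% level. Study period 42 days.

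**Assumptions (not in the documents).** Every patient uses one of two drugs, half on each. One usual dose is 1 mg of drug A or R mg of drug B. The change in weekly doses has SD 2 in both arms, and the intervention lowers it by 1 dose on average, so d = 1/2 = 0.50 in doses. R runs from 2 to 50.

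**1. Loss of precision, with nobody switching.** Each change in doses is multiplied by w, which is 1 or R with equal chance.

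- Mean difference in mg: m = (1 + R)/2
- Mean squared weight: q = (1 + R²)/2
- Variance, control: 4q
- Variance, intervention: (4 + 1)q − m²
- d in mg: m / √(average of the two variances)
- Power: Φ(d × √(33/2) − 1.96)

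For R = 5: m = 3, q = 13, variances 52 and 65 − 9 = 56, average 54, SD 7.35, d = 3/7.35 = 0.41. Power = Φ(0.408 × 4.062 − 1.96) = Φ(−0.30) = 0.38.

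| R | m | Variance control / intervention | d in mg | Power, 33 per arm |
|---|---|---|---|---|
| 1 (same as doses) | 1 | 4 / 4 | 0.50 | 0.53 |
| 2 | 1.5 | 10 / 10.25 | 0.47 | 0.48 |
| 5 | 3 | 52 / 56 | 0.41 | 0.38 |
| 10 | 5.5 | 202 / 222.25 | 0.38 | 0.34 |
| 20 | 10.5 | 802 / 892.25 | 0.36 | 0.31 |
| 50 | 25.5 | 5002 / 5602.25 | 0.35 | 0.30 |

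With equal numbers of doses taken, drug B supplies R/(1 + R) of the pooled total: 67%, 83%, 91% and 95% at R = 2, 5, 10 and 20.

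**2. A switch within one patient.** One dose of B replaced by one dose of A changes the mg by 1/R − 1, which is −50%, −80%, −90% and −95% at R = 2, 5, 10 and 20, with no change in doses. One dose of B replaced by two doses of A doubles the doses, yet the mg change is (2 − R)/R: 0% at R = 2, and −60%, −80% and −90% at R = 5, 10 and 20.

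**3. What one switch does to an arm mean.** Take 5 doses a week, also assumed. One patient moving from B to A changes by −5(R − 1) mg a week, which moves the mean of 33 patients by 5(R − 1)/33. At R = 10 that is 45/33 = 1.36 mg, against an assumed treatment effect of m = 5.5 mg, or 25% of the effect. At R = 2 it is 0.15/1.5 = 10%, and at R = 50 it is 7.42/25.5 = 29%.

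**4. Direction.** If users of A cut 3 doses and users of B add 1, the mean change is 0.5(−3) + 0.5(1) = −1.0 dose. In mg it is 0.5(−3) + 0.5R, which is −0.5 at R = 2 but +1.0 at R = 5 and +3.5 at R = 10.

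**The case against.** The outcome is a change. For a patient who stays on one drug, the change in mg does follow the amount taken. Allocation is randomised, so the drug mix is balanced in expectation. If switching does not differ between arms, unequal strengths mainly add noise. The reversal of sign in step 4 needs users of the two drugs to move in opposite directions, which nothing in the documents suggests. All of this stands.

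It can also be said that the total may only mean scheduled plus as-needed use, that mg might be tabulated by drug, and that a journal article leaves such detail to fuller documents. This is weaker. The article does state the unit and the aggregation across both classes, and a single total is the plain reading. The point concerns a rule that is written down, not one that is absent.

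Three stronger readings are tempting, and the documents do not support them:

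- A reader might infer that the variable measures only which drug is taken, so that the hypothesis cannot be tested at all. The calculation shows lost efficiency and exposure to switching, not an unanswerable question.
- A reader might infer that mixing of drugs is certain. It is to be expected, but no drug list, number of users or switching rate is given.
- A reader might infer that a normal mixed model will fail on a skewed total full of zeros. The linear mixed model is "used to examine the primary and secondary continuous objectives", without naming medication use, and no distribution or share of non-users is reported.

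**Conclusion.** The point holds as a weakness in the definition of one secondary outcome. A pooled mg total weights patients by drug strength and registers switches as changes in consumption. Under the assumptions above, d falls from 0.50 to about 0.47 at R = 2 and 0.35 at R = 50, and power at 33 per arm from about 0.53 to 0.48 and 0.30. A single switch in an arm can move its mean by roughly 10% to 29% of the assumed effect. Such shifts bias the comparison only if switching differs between arms; otherwise they add to the noise.

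The direction of the loss does not depend on the exact values, but its size does. The strength ratios, the even split between drugs, the dose counts and the assumption that every patient is a user are all illustrative. The PSQI primary outcome and the sample size, which was computed for PSQI, are not touched.

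**What to change.** Before unblinded analysis:

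1. Redefine the outcome as the change in total consumption after each drug is converted to a common unit, either defined daily doses or an equivalence table listed in advance. Use this for the between-group test in place of the pooled raw mg total.
2. Add the number of nights with any sedative or hypnotic as a supportive measure, where the diary records intake.
3. Report raw mg only by drug.

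The table must be fixed before allocation is known to the analysts, because a conversion chosen afterwards could depend on the results.

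The cost is the table and a change of wording. Working out milligrams already requires the drug and dose to be known, so new data collection should not be needed, but the diary templates (Additional files 2 and 3) are not shown and this should be checked. There are two downsides. Any conversion is approximate. And Data management {19} lists as-needed medication from the diary and prescriptions from the hospital record, so regular medication may be known as prescribed rather than as taken. That would limit both the converted total and the count of nights, and the report should say so. The change concerns measurement only and alters no treatment rule.
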